## Objectives

### General objective

To evaluate the process, effectiveness and cost-effectiveness of an intervention to reduce social isolation and its consequent negative impact on health of older people.

### Specific objectives

To evaluate the implementation process of the intervention (participant profile, positive and negative aspects of the intervention, barriers and facilitators in its implementation, quality of the intervention, and satisfaction).To assess the impact of the intervention on social support, self-perceived health status, mental health and quality of life among participants, and visits to the primary care center.To determine the cost-effectiveness of the intervention.

## Methods

### Study design

This is a mixed methods multi-approach evaluation that includes:a qualitative evaluation among coordinators and participants who underwent the intervention through in-depth interviews and focus groups, respectively;a quantitative quasi-experimental design, comparing a group of individuals taking part in the intervention (IG) with another group with similar characteristics not receiving the intervention (CG). Data will be collected at the beginning and at the end of the intervention;an economic evaluation, which includes a cost-utility analysis.

### Study setting and participants

#### Qualitative evaluation

The study population will include coordinators of the School of Health (community nurses from the Public Health Agency of Barcelona) and participants who will attend the School of Health in the intervention neighborhoods. In-depth interviews will be carried out with the coordinator of each IG, who will be selected through intentional opinatic sampling (non-randomized sampling in which the researcher selects a sample based on their knowledge about the study and population) [19].

School of Health participants will be adults aged 65 years or older residing in two disadvantaged neighborhoods of Barcelona (Spain) where the School of Health will be implemented. Theoretical sampling will be designed to select participants from the School of Health. For each neighborhood, two groups of participants will be selected according to their risk of experiencing loneliness. The risk of loneliness will be measured through various questions extracted from the National Social Life, Health, and Aging Project (NSHAP) study [20], included in the questionnaire used in the quantitative study. Individuals who report feeling a lack of companionship often, regardless of their cohabitation status (with relatives or alone), will be categorized as ‘at high risk’ and those reporting hardly ever feeling alone and living with relatives will be classified as ‘low risk’. Thus, four focus groups (two per neighborhood) with 6 to 10 assistants will be assembled.

For each focus group, we will select participants providing the widest range of profiles to ensure a variety of discourses according to age, sex, marital status and educational level. Community nurses will be asked about the ability of the selected participants to follow the dynamics of a focus group. Then, the selected participants will be contacted by telephone, informed about the study and asked if they are willing to participate. Those refusing to take part in the study will be replaced by other individuals with similar characteristics. Those who accept to take part in the focus group will have to sign an informed consent form.

#### Quantitative quasi-experimental design

The study population will consist of adults aged 65 years or older residing in the disadvantaged neighborhoods of Barcelona (Spain) selected for the study. The intervention neighborhoods (*n* = 2) and comparison neighborhoods (n = 2) will be selected on a convenience basis, ensuring similar socioeconomic characteristics, including the percentage of people with primary studies or less, unemployment rates and disposable household income rates.

The intervention will be offered to adults aged 65 years or older, living in one of the two selected neighborhoods, and recruited through primary care centers, social services and civic centers for older people. Once individuals have accepted to participate, there will be a pre-registration process that will record their names and telephone numbers. Later, the participants will be contacted by telephone to arrange an appointment, in which the person will be informed individually about the study. After agreement, he/she will sign the informed consent form and complete a questionnaire.

To calculate the sample size, we took into account that 45% of people aged 65 years or more in Barcelona reports fair or poor health [21] and assumed that the intervention would reduce this prevalence by 17 points. Accepting an alpha risk of 0.05% and a power of 80% in a unilateral contrast, and assuming a loss of 10%, we estimated that a theoretical sample of 79 participants in the IG and 79 participants in the CG will be needed.

We expect to recruit 80 individuals in the IG and 80 in the CG. To have similar groups, the recruitment settings (primary care centers, social services and civic centers) would be taken into account, by selecting the same percentage of people from each setting.

The exclusion criteria are the following:Participants with difficulties in maintaining participation for 6 months.Participants with difficulties in understanding or expressing themselves in Spanish or Catalan.

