### Description of the intervention

The intervention “School of Health for Older People” consists of 22 weekly group sessions of 1.5 h each, in which issues related to health—including both biological and psychological issues—and social topics, are discussed. Attendance is free and the sessions will be held in community centers of the selected neighborhoods. In addition to helping participants learn about different health issues, the intervention encourages interaction among participants and works on skills in different fields, such as nutrition, management of emotions, self-medication, sexuality or physical activity. Furthermore, some sessions included visits to public spaces of the neighborhood and leisure activities adapted to older people.

Furthermore, most sessions are led by professionals who are experts on the topic covered and work in the neighborhood (professionals from the health services, social services, markets or neighborhood associations), making it easier to inform participants of the neighborhood’s available resources. The aim of the intervention is to decrease social isolation and loneliness and, therefore, to improve mental health, self-perceived health and wellbeing (see the explanatory model of the potential effects of the intervention in Fig. 2).

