#### Quantitative quasi-experimental design

A descriptive analysis will be conducted to rule out significant differences between baseline characteristics (sociodemographic variables and outcomes studied) in the IG and the CG. The chi-square test will be used to compare qualitative variables. Continuous variables with normal distribution will be compared using the Student t test, and the Mann-Whitney U test will be used in non-normally distributed variables. In case of differences, a further multivariate effectiveness analysis will be conducted adjusting for these variables.

Further descriptive analyses will be conducted for results at baseline and at follow-up. Categorical outcomes will be described through percentages, and continuous outcomes will be described through mean scores and standard deviations or the median and interquartile range, as required. Differences between pre- and post-intervention measurements will be assessed and compared using the McNemar test, paired t-test, or sign test, according to the type of variable and distribution.

To assess the effectiveness of the intervention, a two-sample McNemar test will first be conducted to analyze differences in changes in pre- and post-intervention results between the IG and the CG for each main outcome. In those outcomes showing differences between the groups at the baseline measurement, Poisson regression models with robust variance will be built. In each model, the independent variables will be the group (IG or CG), the pre-intervention measurements for the outcome assessed and any relevant characteristics that differ between the groups at the baseline assessment.

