#### Economic evaluation

The incremental cost-utility ratio (ICUR) will be calculated by subtracting the costs of the CG from the costs of the IG and dividing the result by the QALYs for the CG subtracted from the QALYs for the IG. The incremental costs and the incremental utility will be modeled by generalized linear models, taking into account the distribution of both costs and effects.

To estimate the uncertainty related to the ICUR, we will calculate 95% confidence intervals for the mean cost differences using the non-parametric confidence interval. Bootstrapping with 1000 replications will be performed.

Bootstrapped cost effects pairs will be plotted on cost-effectiveness planes and used to estimate cost-utility acceptability curves (CUACs). In the cost-utility planes, the ‘x’ axis represents the difference in QALYs and the ‘y’ axis the difference in costs. CUACs demonstrate the probability that an intervention is cost effective at a specific ceiling ratio, which is the amount of money society is willing to pay to gain one extra unit of effect. Willingness to pay values will range from 0€ to 50,000€ [26].

The robustness of the estimates will be addressed by conducting sensitivity analyses. This analysis will comprise a variation in the unit cost of the primary care medical or nurse visits, in the costs of the workshop leaders’ hourly wage and in the venue rental cost.

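### Exposure follows neighbourhood (two per arm) and delivery is in groups, but the sample size and main test assume independent individuals and the limitations omit clustering

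*Protocol article*

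**What the plan says.** All references are to the protocol article.

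- **Allocation** (Study setting and participants, Quantitative quasi-experimental design). Two intervention neighbourhoods and "comparison neighborhoods (n = 2) will be selected on a convenience basis". The programme is offered to people "living in one of the two selected neighborhoods, and recruited through primary care centers, social services and civic centers for older people". Areas are matched by "ensuring similar socioeconomic characteristics, including the percentage of people with primary studies or less, unemployment rates and disposable household income rates".
- **Delivery** (Description of the intervention). The programme "consists of 22 weekly group sessions of 1.5 h each", and "the intervention encourages interaction among participants".
- **Sample size** (same section as allocation). It starts from the figure that "45% of people aged 65 years or more in Barcelona reports fair or poor health" and assumes a 17-point reduction, a one-sided test, 80% power and 10% loss. The result is 79 per group, with a target of 80. No ICC or design effect appears.
- **Effectiveness analysis** (Data analysis, Quantitative quasi-experimental design). A two-sample McNemar test comes first. Poisson models with robust variance follow for outcomes that differ at baseline. In these, "the independent variables will be the group (IG or CG), the pre-intervention measurements for the outcome assessed", together with characteristics that differ at baseline. The unit for the robust variance is not stated.
- **Economic analysis** (Data analysis, Economic evaluation). "Bootstrapping with 1000 replications will be performed"; the resampling unit is not stated.
- **Neighbourhood** is recorded (Sociodemographic variables) but given no role as a clustering unit.
- **Strengths and limitations** acknowledges possible differences between groups and proposes adjustment. It does not mention clustering or the number of areas.

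**The concern.** People in one neighbourhood share services, primary care and local events. In the intervention group they also share sessions and each other's company, which is part of how the programme is meant to work. Correlated outcomes are therefore to be expected. Two things are at stake.

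**Precision.** If outcomes are correlated within neighbourhoods, an analysis of independent individuals gives standard errors that are too small, too many false positives and less real power than stated.

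**Attribution.** Every neighbourhood belongs wholly to one group. With two areas per arm, a change peculiar to one area during the study looks the same as a programme effect. Primary care visits, one of the main outcomes, are an obvious example because they depend on local practice.

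**Working it through.** **1. The plan's own figure.** Inputs: p1 = 0.45, p2 = 0.45 − 0.17 = 0.28, one-sided, power 0.80, 10% loss. Alpha is printed as 0.05% and is read here as 0.05. The mean proportion is 0.365.

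n = [1.645·√(2·0.365·0.635) + 0.842·√(0.45·0.55 + 0.28·0.72)]² / 0.17² = [1.645·0.6808 + 0.842·0.6701]² / 0.0289 ≈ 98.1, so 99 evaluable per arm. With 10% loss, 99/0.9 = 110.

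The stated 79 is not reproduced. That is a separate error, but it sets the starting point. The target of 80 less 10% leaves 72 evaluable per arm:

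Power = Φ[(0.17·√72 − 1.645·0.6808)/0.6701] = Φ(0.48) ≈ 68%. With all 80 retained it would be about 72%.

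**2. Adding clustering.** Assumptions: equal neighbourhoods of m = 72/2 = 36 evaluable people, and the same ICC in both arms. The documents give no ICC.

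- Design effect: DE = 1 + (m − 1)·ICC
- Effective n per arm: 72/DE
- Power of a test that allows for the clustering: the formula in step 1 at the effective n
- True error of a nominal one-sided 5% test that ignores clustering: 1 − Φ(1.645/√DE)

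| ICC | DE | Effective n per arm | Power | True one-sided error |
|---|---|---|---|---|
| 0 | 1.00 | 72 | 68% | 5.0% |
| 0.01 | 1.35 | 53 | 57% | 7.8% |
| 0.02 | 1.70 | 42 | 49% | 10.4% |
| 0.05 | 2.75 | 26 | 35% | 16.1% |

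These powers treat the ICC as known. A comparison of the four neighbourhood means has 2 degrees of freedom (one-sided critical value 2.92 instead of 1.645), and its power is about 35%, 30% and 23% at the three positive ICCs.

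**3. Clustering in the intervention group only.** The variance of the difference is then inflated by about (1 + DE)/2, that is 1.175, 1.35 and 1.875. The one-sided error becomes 1 − Φ(1.645/√1.175) = 6.5%, then 7.8% and 11.5%.

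**4. Would more people per neighbourhood solve it?** As m grows, the effective n per arm approaches 2/ICC. To reach 99 this needs ICC ≤ 2/99 ≈ 0.020. Above that, two areas per arm cannot give 80% power at any recruitment.

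**5. Would resampling people within neighbourhoods repair the bootstrap?** Take unit variance, 80 per arm, m = 40 and ICC 0.05. The true standard deviation of the difference is √(2·2.95/80) = 0.272. Ignoring clusters gives √(2/80) = 0.158. Resampling within fixed neighbourhoods gives about √(2·0.95/80) = 0.154, because it leaves out the between-neighbourhood variance. It does not help.

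**The case against.** **The article is condensed, and silence is not a statement.** This stands in part. A reader might infer that the Poisson models and the bootstrap certainly treat all participants as independent. The text does not say so: it leaves the unit of the robust variance and of the resampling unstated, and a fuller plan could specify them. The firm evidence is the sample size and the McNemar test as named. A fuller plan could not change the number of areas or the stated sample size. A variance clustered on four neighbourhoods would also be unreliable.

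**The ICC is assumed.** This stands. Outcomes analysed as change or adjusted for baseline may have a smaller ICC, and the comparison group has no sessions. Step 3 shows smaller effects if only the intervention group is clustered. The number and size of session groups are not given. The direction is the same for every positive ICC.

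**Group differences are already handled.** This stands in part. Area matching, equal shares from each recruitment setting, baseline adjustment and the quasi-experimental caveat all reduce differences in level. None of them removes change specific to a neighbourhood during the study.

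**Not all the lost power is due to clustering.** This stands. A reader might blame clustering for the whole fall from 80%. The first 12 points or so (80% to 68%) come from the sample-size error. Clustering takes about another 11 points at ICC 0.01, 19 at 0.02 and 33 at 0.05.

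**Conclusion.** The point holds. The sizing and the named main test make no allowance for neighbourhood or session-group correlation, and the limitations do not disclose it. With 36 evaluable people per neighbourhood and ICCs of 0.01 to 0.05 in both arms, power is about 57% to 35%, against 68% without clustering and 80% as stated. The one-sided error is about 7.8% to 16.1%. These figures rest on an assumed ICC, equal neighbourhoods and an alpha of 5%. They are given one-sided because that is the only sidedness the article states.

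A reader might also infer that a result which stays significant after its standard errors are inflated would show that the programme works elsewhere. The documents do not support that. The areas are few and chosen by convenience, and inflating a standard error does not separate programme from place.

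The matter should be corrected. It does not by itself invalidate the study.

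**What to change.** 1. Restate power over a range of ICCs, for example 0.01 to 0.05, starting from the corrected unclustered figure.
2. Report each main result, and the cost and QALY differences, a second time with standard errors multiplied by √DE over the same range (1.16, 1.30 and 1.66 at m = 36 for ICC 0.01, 0.02 and 0.05).
3. Show the four neighbourhood-level baseline-adjusted means, so that readers can see whether both intervention areas moved in the same direction.
4. State the unit of the robust variance and of the bootstrap. Do not rely on ordinary cluster-robust errors with four clusters, or on resampling people within neighbourhoods.
5. Add to the limitations that, with two neighbourhoods per arm, a programme effect cannot be separated from neighbourhood-specific change. Conclusions are therefore limited to these neighbourhoods, whatever the sensitivity analysis shows.

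The cost is a sensitivity analysis and some wording, with no extra participants or sites. The downside is wider intervals and a less favourable stated power.

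### The study is planned on a one-sided contrast with a misprinted alpha, the effectiveness analysis fixes neither side nor level, and the stated 80% power is not reached on either reading

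*Protocol article*

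**What the plan says.** All of the planning inputs stand in one paragraph of the Protocol article, under Study setting and participants, Quantitative quasi-experimental design:

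- Reference prevalence: "45% of people aged 65 years or more in Barcelona reports fair or poor health".
- Effect: the authors "assumed that the intervention would reduce this prevalence by 17 points", that is, from 45% to 28%.
- Error rates: "Accepting an alpha risk of 0.05% and a power of 80% in a unilateral contrast".
- Loss to follow-up of 10%, a resulting requirement of 79 per group, and an expected recruitment of 80 per group.

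The Hypothesis section is directional. It predicts improvement in social support, mental health, general health and quality of life, and fewer primary care visits in the intervention group.

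Under Data analysis, Quantitative quasi-experimental design, the first between-group step is that "a two-sample McNemar test will first be conducted to analyze differences in changes" for each main outcome. Robust Poisson models follow where the groups differ at baseline. No side and no significance level is given for any of these tests.

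**The concern.** The only error rule in the article is the one in the sample-size paragraph. It is one-sided, its alpha is printed as a value that cannot have been intended, and the analysis section does not repeat it. The reader cannot tell what a significant improvement will mean when results are reported.

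Two branches are possible, and the article does not show which one applies:

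- The one-sided 5% rule governs the effectiveness tests. A one-sided p of 0.04 would then count as success, on each of several main outcomes, where a two-sided 5% test would not declare it.
- The tests are run in their conventional two-sided form. The words "a power of 80% in a unilateral contrast" then describe a test that nobody performs, and the power belongs to that other test.

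Either way, a reader who relies on 80% power to interpret a null result would be misled if the sample does not deliver it.

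**Working it through.** **Inputs.** From the sample-size paragraph: p1 = 0.45; p2 = 0.45 − 0.17 = 0.28; power 0.80; loss 10%; equal groups. Assumption: the printed 0.05% means 5%. The literal value is also tried.

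**Formula.** Two independent proportions, pooled variance under the null:

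n = [z(α)·√(2·p̄·(1−p̄)) + z(power)·√(p1(1−p1) + p2(1−p2))]² / (p1−p2)²

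Here p̄ = 0.365, so √(2 × 0.365 × 0.635) = 0.6808. The second root is √(0.2475 + 0.2016) = 0.6701. The denominator is 0.17² = 0.0289, and z(0.80) = 0.8416.

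**Step 1: try to reproduce 79.**

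- One-sided 5% (z = 1.645): (1.1199 + 0.5640)² / 0.0289 = 98.1, so 99 evaluable; 99 / 0.9 = 110 per group.
- Two-sided 5% (z = 1.960): (1.3344 + 0.5640)² / 0.0289 = 124.7, so 125 evaluable; 125 / 0.9 = 138.9, so 139 per group.
- One-sided at the literal 0.05% (z = 3.291): 273 evaluable; 273 / 0.9 = 303.3, so 304 per group.

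Variants for one-sided 5%, after loss: 123 with continuity correction, about 107 with unpooled variance, about 109 with the arcsine method. No two-group version tried gives 79. The literal alpha is furthest from it, which supports reading it as a misprint for 5%.

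**Step 2: power of the sample as planned.** 79 × 0.9 = 71.1, so about 71 evaluable per group.

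Power = Φ{[0.17·√n − z(α) × 0.6808] / 0.6701}

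- n = 71, one-sided 5%: (1.4324 − 1.1199) / 0.6701 = 0.466, power 0.68.
- n = 71, two-sided 5%: (1.4324 − 1.3344) / 0.6701 = 0.146, power 0.56.

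| Test | Evaluable needed for 80% | With 10% loss | Power at 71 | Power at 80 |
|---|---|---|---|---|
| One-sided 5% | 99 | 110 | 68% | 72.5% |
| Two-sided 5% | 125 | 139 | 56% | 61% |
| One-sided 0.05% (literal) | 273 | 304 | 11% | 14% |

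The column for 80 supposes that all 80 recruits are evaluable. With 10% loss, 80 become 72, and power is 68% one-sided and 56% two-sided.

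**Step 3: favourable-direction error.** A two-sided 5% test puts 5% / 2 = 2.5% in the direction of benefit. A one-sided 5% test puts all 5% there. The ratio is 2 for each outcome tested.

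**The case against.** The strongest reply is that nothing here is contradictory. The Hypothesis section is directional, and a one-sided contrast matches it. The analysis section is silent on side and level, and an article may leave that to the full protocol or analysis plan. Both points are fair, and silence alone would not be a finding. What remains is what the article does state: a one-sided contrast, an impossible alpha, and a power of 80% that its own inputs do not support. The directional hypothesis says what the authors expect. It does not explain why benefit should be claimed at a more lenient level than usual.

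Several stronger readings are tempting but not supported:

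- **That the named tests are two-sided by construction.** They are not. The paired t, sign and Wald tests can be run one-sided, and so can McNemar in its exact or signed-root form. The chi-square test is named for baseline comparisons. The accurate statement is that the side is unspecified and the convention is two-sided.
- **That the economic evaluation contradicts the one-sided plan.** It says "we will calculate 95% confidence intervals for the mean cost differences". That interval is for costs and does not bear on an effectiveness test.
- **That visits may well rise because sessions publicise local resources.** The Description of the intervention names speakers from health services, social services, markets and neighbourhood associations, and says nothing about primary care use. The inference is speculative.
- **That the false-positive rate is doubled.** This holds only if 5% was meant and only if the one-sided rule carries over. Read literally, 0.05% would be far stricter than 2.5%.
- **That the choice of side explains the low sample size.** It does not: even the lenient one-sided test needs 110 per group.

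**Conclusion.** The point holds in a limited form. The planning paragraph adopts a one-sided contrast with no justification beyond the directional hypothesis and misprints alpha, and nothing in the article says whether that rule governs the effectiveness tests. The consequence is either a 5% instead of a 2.5% favourable-direction error per outcome, or a power statement for a test other than the one run. In both cases the stated power is too high: about 68% one-sided, or 56% two-sided, against 80%. The side accounts for about 12 percentage points of that gap; the rest is there even on the one-sided reading.

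This rests on three assumptions: that 5% is the intended alpha, that 10% of 79 are lost, and that power is judged for a simple comparison of 45% with 28% between independent groups, as the planning inputs define it. The power of the planned test on changes would also depend on the within-person correlation, which the article does not give.

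**What to change.** - In the sample-size paragraph, correct the printed alpha to 5% and replace the one-sided contrast by a two-sided one.
- In the quantitative data analysis section, state that every between-group effectiveness comparison is two-sided at 5%.
- Replace the claim of 80% by the power of the fixed sample: about 56% with 71 evaluable per group, and 61% if all 80 are evaluable. Say that these figures are for 45% versus 28%.

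The cost is wording and a visibly less favourable power statement. Recruitment stays at 80 per group. Reaching 80% power two-sided on the stated inputs would take 139 per group, so keeping the sample means accepting and reporting the lower power. In return, the standard for claiming benefit on each main outcome is fixed, and null results can be read against the power that the study has.

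### The 79 per group does not follow from its stated inputs: an unpaired one-sided 5% comparison of 45% with 28% needs about 99 evaluable (110 enrolled), and 79 enrolled gives about 68% power

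*Protocol article*

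**What the plan says.** The whole calculation is in the Protocol article, Methods, Study setting and participants, Quantitative quasi-experimental design. It starts from the premise that "45% of people aged 65 years or more in Barcelona reports fair or poor health" and "assumed that the intervention would reduce this prevalence by 17 points", which puts the intervention group at 28%. The error rates are given as "a power of 80% in a unilateral contrast", with an alpha risk printed as 0.05% and an allowance of 10% for loss. The result is that "we estimated that a theoretical sample of 79 participants in the IG and 79 participants in the CG will be needed". The recruitment target is set just above it: "We expect to recruit 80 individuals in the IG and 80 in the CG".

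The article gives no formula, pre-post correlation or proportion of discordant pairs.

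**The concern.** The paragraph gives every input that a standard two-proportion calculation needs, so its result can be checked. A 17-point difference starting from 45% is moderate, and 71 evaluable people per group looked too few to detect it with 80% power at a one-sided 5% level.

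This is the article's only quantitative justification of the sample size. If the 80% is wrong, a non-significant result on this endpoint could be taken as coming from a study with a 20% chance of missing the assumed effect, when that chance is nearer one in three. The Background also offers the protocol as a tool for evaluating future interventions, so the number may be copied.

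**Working it through.** **Inputs (all from the sample-size paragraph).** p1 = 0.45; p2 = 0.45 − 0.17 = 0.28; one-sided test; power 80%; loss 10%; equal groups. Alpha is taken as 0.05, because the printed 0.05% is evidently a slip.

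**Trying to reproduce 79.** The pooled-variance formula per group is

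n = [z(1−α)·√(2p̄(1−p̄)) + z(power)·√(p1(1−p1) + p2(1−p2))]² / (p1 − p2)²

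- p̄ = (0.45 + 0.28)/2 = 0.365, so √(2 × 0.365 × 0.635) = 0.6808
- √(0.45 × 0.55 + 0.28 × 0.72) = √0.4491 = 0.6701
- z(0.95) = 1.645 and z(0.80) = 0.842
- n = (1.645 × 0.6808 + 0.842 × 0.6701)² / 0.17² = 98.1, so 99 evaluable
- With 10% loss: 99 / 0.9 = 110 enrolled

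The stated figure is not reproduced. The choice of formula does not explain the gap:

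| Method (one-sided 5%, 80% power) | Evaluable per group | Enrolled with 10% loss |
|---|---|---|
| Pooled variance | 99 | 110 |
| Unpooled variance | 97 | 107 |
| Arcsine | 98 | 109 |
| Continuity-corrected | 110 | 123 |
| **Stated in the article** | about 71 (79 × 0.9) | **79** |

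**What does match 79.** With one-sided alpha 10%, z = 1.282 and n = (1.282 × 0.6808 + 0.842 × 0.6701)² / 0.17² = 71.4. Then 71.4 / 0.9 = 79.3. A 20-point drop (45% to 25%) at one-sided 5% gives 70 evaluable and 78 enrolled. A within-group paired calculation with a discordant proportion of about 0.34 gives about 71 pairs. The article states none of these three inputs.

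**Power delivered for the stated 17 points.** Power = Φ{[0.17·√n − z(1−α)·0.6808] / 0.6701}.

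For n = 71, one-sided 5%: (0.17 × 8.426 − 1.120) / 0.6701 = 0.466, and Φ(0.466) = 68.0%.

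| Evaluable per group | One-sided 5% | Two-sided 5% |
|---|---|---|
| 71 (79 enrolled, 10% loss) | 68.0% | 55.8% |
| 72 (80 enrolled, 10% loss) | 68.5% | 56.4% |
| 80 (no loss at all) | 72.5% | 60.9% |

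**Detectable reduction at 80% power with 71 per group.** 19.8 points one-sided; 22.1 points two-sided.

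**How far the planned analysis could move this.** Both checks below need a pre-post correlation ρ. The article gives none, so 0.3 to 0.6 is an assumed range. Both are normal approximations at 71 per group.

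- *Comparison of changes*, with both groups at 45% at baseline and the intervention group at 28% afterwards, one-sided 5%: about 55% power at ρ = 0.3, 67% at 0.5 and 75% at 0.6.
- *Adjustment for the baseline value*, with the variance reduced by the factor 1 − ρ²: power = Φ{0.17·√(71/(1−ρ²)) / 0.6701 − z(1−α)}. This gives 72% at ρ = 0.3, 79% at 0.5 and 85% at 0.6 one-sided, and 61%, 69% and 76% two-sided.

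**The case against.** The strongest reply is that 68% is the power of a test the study may not run. The Data analysis section tests effectiveness with a two-sample McNemar test on changes, and with robust Poisson regression including the pre-intervention value for outcomes that differ at baseline. Power under either depends on a correlation that the article does not give. This stands as a limit on what can be claimed. A reader might infer that the study's true power is 68%, and the document does not support that. It does not rescue the 79 either. The sample-size paragraph is worded as a comparison of prevalences and has no paired input, and over the range tried the comparison of changes stays below 80%. Baseline adjustment could pass 80% one-sided at the upper end of that range, but the article plans it only conditionally.

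A reader might also infer that a one-sided calculation clashes with two-sided tests in the analysis. The document does not show this. Its chi-square test is assigned to baseline comparability only. The Hypothesis section is directional, and the analysis section does not say whether its tests are one- or two-sided, a detail often left to an analysis plan. The two-sided figures are therefore conditional.

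The printed alpha could be taken literally. That would require 273 evaluable per group, but nobody is likely to have meant it, and it adds nothing to the case beyond a misprint to correct.

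Finally, fair or poor health is not named under Main outcomes, although self-perceived health is among the specific objectives. The 80% claim therefore says little about power for the listed main outcomes. This limits the consequences, but the arithmetic is unaffected.

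**Conclusion.** The sample-size statement is wrong as written. On its own inputs, with alpha read as 5%, it should give about 99 evaluable and 110 enrolled per group, so 79 is short by 110 − 79 = 31 per group. For the unpaired one-sided comparison of 45% with 28%, the delivered power is about 68% after the assumed 10% loss and about 73% with no loss. The chance of missing the assumed effect is thus about 32% rather than 20%.

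This rests on reading the inputs as a two-group comparison of prevalences at the end of the study, which is how the paragraph is worded. The conclusion does not depend on which standard formula is used. The source of the 79 cannot be established from the document: an alpha of 10% matches it closely, but so do other unstated inputs.

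**What to change.** Keep the recruitment of 80 per group and rewrite the sample-size paragraph:

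- Print alpha as 5% (0.05).
- Replace the 80% power claim with the delivered figure, about 68% one-sided for a 17-point reduction, or with the reduction detectable at 80% power, about 20 points one-sided. Both assume 71 evaluable per group.
- Say that the figure refers to an unpaired comparison of prevalences.
- State whether the final tests are one- or two-sided. If two-sided, use about 56% and about 22 points.
- If a gain from baseline adjustment is mentioned, give it as an assumption with its range: roughly 72% to 85% one-sided, or 61% to 76% two-sided, for pre-post correlations of 0.3 to 0.6.

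This is a text correction with no added participants. By the article's own timeline the intervention ran in January to June 2015, so a larger sample is not in question. The cost is that the stated power becomes less favourable.
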